### Study design and setting

2.1

A multicenter, outpatient department (OPD)-based, prospective observational study of patients diagnosed with MCI or dementia is being conducted from April 2018 to December 2018, as a part of a Registry for Korean Medicine and Western Medicine Collaborative Treatment (REKOMENT study). Participants are recruited from 6 university-affiliated hospitals and 1 national medical center, which are participating in the “second-stage pilot project of KM-WM collaborative treatments.” The participants receive treatments from practitioners of KM and/or WM as they would in the real world, and are asked to undergo additional assessments. We will analyze the type of treatment (collaborative or sole treatment), changes in assessment scores, and costs for treatment of MCI/dementia. A comparative observational study design has been adopted to compare the participants in a collaborative treatment (CT) group and those in a sole treatment (ST) group. The study flowchart can be found in the flow diagram (Fig. 1).

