Appropriate standardization procedures have been implemented to minimize differences between evaluators in the different institutions as much as possible. KM or WM physicians with >1 year of clinical experience are in charge of the clinical evaluations. The QoL assessment is based on responses of patients or their guardians to a questionnaire. The patients and/or guardians are allowed to ask the researcher questions if there are difficulties in understanding the meaning of a question. However, they are required to respond to the questions independently without intervention from the researchers.

Administrative data from each institution will be used to determine the costs of MCI/dementia treatments, and the type and frequency of collaborative treatment. Data obtained from the HIRA include medical expenses of the patients, the duration of medical use, and the type of medical services used by the patients.

The time schedule for data collection is presented in Table 1. All collected data will be recorded using iCReaT, which is a type of electronic case report form supplied by the Korea National Institute of Health. The study procedures including the data collection and management will be monitored by the Monitoring Center for Korean Medicine and Western Medicine Collaboration, which is governed by the Ministry of Health and Welfare.

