### Treatments

2.6

The participants receive treatment for MCI/dementia, mostly based on their practitioners’ clinical opinions; thus, there is no fixed treatment for the study. The participants can freely choose any type of WM and/or KM treatment method. When a participant wishes to receive both WM and KM treatment, the practitioner of 1 type of medicine used for the patient's treatment will make a “request for a collaborative treatment” to a practitioner of the other type of medicine. The participants can freely decide the type of treatment in consultation with their practitioners at any time, as with general care. All treatments that the participants receive will be recorded and monitored.

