### Statistical and analytical plans

2.8

Baseline characteristics and disease progression will be compared between the CT and ST groups. All continuous variables will be tested to confirm normality. Student *t* tests or Wilcoxon rank sum tests will then be used to compare the means of the 2 groups. Categorical data will be analyzed using *χ*^2^ or Fisher exact tests. Per-protocol and intention-to-treat (ITT) analyses will be used to assess all effectiveness and cost-effectiveness data. Missing volume, pattern, and mechanisms will be analyzed before the ITT analysis. If the missing mechanism is identified as missing completely at random or missing at random, as defined by Rubin,^[43]^ the multiple imputation method will be used to replicate the missing data. Scores on the S-IADL, Barthel-ADL, S-GDpS, NPI-Q, MoCA-K, MMSE, CDR, GDS, and QoL as measured by the EQ-5D and EQ-VAS, and the use of long-term care service will be compared between the 2 groups for effectiveness analysis. Means and 95% confidence intervals for continuous variables and frequencies and percentages for categorical variables will also be calculated. All statistical analyses will be performed using 2-tailed tests at a significance level of .05. In the economic evaluation, the ICER results will be analyzed deterministically using mean values, and the statistical significance of differences in ICER will be determined using the bootstrapping method. CEAC will also be analyzed and reported along with the meaningful ranges for the national thresholds. Stata MP version 14 (StataCorp LLC, TX) and SAS version 9.4 (SAS Institute Inc., Cary, NC) will be used for all of the aformentioned analyses.

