### Ethics and dissemination

2.9

This study has been approved by the institutional review boards (IRBs) of National Medical Center (H-1803–088–002), Wonkwang University Sanbon Hospital (WMCSB 201802-11), Dongguk University Bundang Oriental Hospital (DUBHIRB2018-0001), Gil Korean Medicine Hospital of Gachon University (18-103), Wonkwang University Jeonju Korean Medicine Hospital (WUJKMH-IRB-2018-0001), Gwangju Oriental Hospital of Wonkwang University (2018/3), and Daejeon University Dunsan Korean Medicine Hospital (DJDSKH-18-BM-05). The protocol for this study has been registered at the clinical research information service (KCT0002868).

A KMD will ask participants who have decided to voluntarily enroll in the study to submit written consent. All data obtained from the participants will be secured. Hard copies will be stored in double-locked locations and soft copies will be saved in memory devices not connected to the internet also stored in double-locked locations. The corresponding author will have access to the final dataset. All participants will be protected and respected according to the Declaration of Helsinki and related laws and regulations. The present findings will be disseminated in a report published in a peer-reviewed journal.

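### Section 2.8 compares CT with ST across seven hospitals without a hospital term; if the CT share differs by hospital, the contrast is biased and its standard errors are too small

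*Protocol article*

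**What the plan says.** Section 2.8 fixes the comparison. Continuous variables are checked for normality, and then Student t or "Wilcoxon rank sum tests will then be used to compare the means of the 2 groups". Categorical data get chi-square "or Fisher exact tests. Per-protocol and intention-to-treat (ITT) analyses will be used to assess all effectiveness and cost-effectiveness data". The error level is common to all: "All statistical analyses will be performed using 2-tailed tests at a significance level of .05". The ICER is computed from mean values, with bootstrapping for its uncertainty. Hospital appears nowhere in the section as stratum, covariate or cluster, and no resampling unit is given.

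The data structure is described elsewhere in the article:

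- Section 2.1: "Participants are recruited from 6 university-affiliated hospitals and 1 national medical center".
- Section 2.9: five of the seven ethics approvals are for sites named as Korean medicine or Oriental hospitals, among them "Gil Korean Medicine Hospital of Gachon University (18-103), Wonkwang University Jeonju Korean Medicine Hospital". The other two are the national medical center and one university hospital.
- Section 2.6: "The participants can freely choose any type of WM and/or KM treatment method". Participants may also change treatment type at any time.
- Section 2.4: clinical ratings are made by KM or WM physicians, and standardization is meant to "minimize differences between evaluators in the different institutions as much as possible". Costs come partly from each institution's administrative data.
- Abstract, Method/design: ST pools patients on WM alone with patients on KM alone.

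**The concern.** Treatment is not randomised, and nothing in the design balances CT and ST within a hospital. Two consequences follow if some hospitals supply mostly CT patients and others mostly ST patients.

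First, bias. Whatever differs between those hospitals (price level, patient course, local practice, a change in rating between visits) is counted as an effect of collaboration.

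Second, precision. Outcomes within a hospital are correlated, and a pooled test ignores this. When treatment share varies by hospital, its standard error is too small.

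The Discussion treats the choice of institutions only as a limit on generalisability, not as a source of error in the CT-ST contrast. Since the authors want the results to inform how care for dementia and MCI is organised, a hospital difference reported as an effect of collaboration would matter.

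**Working it through.** **The plan's own figure.** Section 2.7 wants 120 complete patients and allows for 20% missing: 120 / (1 - 0.20) = 150, which reproduces. The rise to 180 has no formula. The article gives no effect size, SD, within-hospital correlation (ICC) or CT share by hospital, so the size of the problem can only be shown over assumed ranges.

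**Type I error.** Inputs from the article: 120 completers, 7 hospitals, two-sided 5%. Assumed: equal hospitals (120 / 7 = 17.1 patients each), a random hospital effect with ICC 0.05 or 0.10, and the CT shares below. For each scenario 20,000 datasets without any treatment effect were simulated, so a 5% rate has a simulation margin of about 1.96 × √(0.05 × 0.95 / 20,000) = 0.3 percentage points. The pooled t test was set against the same contrast with hospital as a fixed effect. The last column is the true SD of the CT-ST difference divided by the average pooled standard error.

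| CT share by hospital | Pooled test, ICC 0.05 / 0.10 | Hospital-adjusted, ICC 0.05 / 0.10 | True SD / pooled SE |
|---|---|---|---|
| 50% everywhere | 5.1% / 5.1% | 4.8% / 5.2% | 1.00 / 1.01 |
| 30% to 70% | 5.7% / 5.9% | 5.1% / 4.9% | 1.03 / 1.04 |
| 30% in two, 70% in five | 6.0% / 7.4% | 5.0% / 5.0% | 1.05 / 1.11 |
| 10% to 90% | 7.9% / 11.3% | 5.1% / 5.2% | 1.12 / 1.25 |
| 10% in two, 80% in five | 9.0% / 13.2% | 5.1% / 5.1% | 1.16 / 1.31 |
| Fully determined by hospital | 15.0% / 22.9% | not estimable | 1.37 / 1.65 |

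The last row agrees with the design-effect formula 1 + (m - 1) × ICC at m = 17.1. This gives 1.81 and 2.61, and 2 × P(Z > 1.96 / √DE) = 14.5% and 22.5%. The formula fits only that row; where both treatment types occur within hospitals it overstates the inflation. At ICC 0.01 the pooled test stays between 4.9% and 6.7% in all rows.

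**Bias.** Suppose the five KM-named hospitals differ from the other two by 0.5 SD in the analysed quantity (a cost, a QALY or a true change score). Let a be the CT share in the five and b in the two, with equal hospital sizes. The bias in CT-ST is

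0.5 × [5a / (5a + 2b) - 5(1 - a) / (5(1 - a) + 2(1 - b))].

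- a = b = 50%: 0.5 × (0.714 - 0.714) = 0
- a = 60%, b = 40%: 0.5 × (0.789 - 0.625) = 0.08 SD
- a = 70%, b = 30%: 0.5 × (0.854 - 0.517) = 0.17 SD
- a = 80%, b = 10%: 0.5 × (0.952 - 0.357) = 0.30 SD

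**Which outcomes are exposed.** Sections 2.5.1.1 and 2.5.1.2 define the QoL and cognitive outcomes as changes from baseline. A constant offset k at one hospital drops out: (follow-up + k) - (baseline + k) = follow-up - baseline. Differing true change and drift in rating remain. Costs, and QALYs by area under the curve (section 2.5.2), are not defined as changes, so hospital differences in level pass straight through.

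**The case against.** Several points on the other side stand.

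- A reader might infer from the hospital names that treatment type follows hospital. The documents do not support this. ST contains both WM-only and KM-only patients, so a KM name suggests at most how ST splits, not the CT share, which is what biases CT-ST. Section 2.9 lists approvals, not services, and the Discussion describes all sites as comparatively well prepared for collaboration.
- A reader might also infer that each hospital's scoring habit contaminates the primary outcomes. As shown, a constant habit largely cancels in change scores. Section 2.4 also has patients or guardians answer the QoL questionnaires without researcher involvement, which leaves evaluator style little route into them.
- Within-hospital correlation alone does not make the error bars too narrow: with equal shares the pooled test holds about 5%. The 15% to 23% figures need hospital to determine treatment type, which sits poorly with free choice.
- Centre terms and resampling units are often left to an analysis plan, which is not shown here. This carries less weight, because section 2.8 does more than stay silent: it names pooled two-sample tests and a raw-mean ICER as the methods for a non-randomised multicentre comparison.

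**Conclusion.** The point holds as a conditional one. The method stated in section 2.8 is valid with respect to hospital only if the CT share is about the same in all seven hospitals, and nothing in the design secures that. With shares of 30% to 70% the inflation is slight (5.7% to 5.9%); with 10% to 90% it is moderate (about 8% to 11%); only full determination by hospital gives 15% to 23%. For an assumed 0.5 SD hospital difference the bias runs from 0 to 0.30 SD across the shares considered. All of this rests on assumed ICCs, shares and offsets, since the article gives none. The documents do not show that the CT share differs by hospital, or that the planned intervals are certainly too narrow. Costs, QALYs and therefore the ICER are most exposed; the change scores are less so. The change is worth making because it is cheap and, where both treatment types occur within hospitals, held type I error at 4.7% to 5.2% in every scenario and ICC simulated.

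**What to change.** In section 2.8:

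1. Estimate each effectiveness, cost and QALY difference from a model with hospital as a fixed effect, plus the baseline score where there is one, or from a hospital-stratified test.
2. Compute the ICER and CEAC from these hospital-adjusted cost and QALY differences. Draw bootstrap samples within hospital and group, and refit the model in each. Stratifying the resampling alone is not enough: it changes the variance but leaves an ICER from raw means confounded by hospital price and practice.
3. Tabulate CT, WM-only and KM-only counts by hospital.
4. Report the unadjusted comparison as a sensitivity analysis.

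The cost is analysis wording and up to six degrees of freedom (seven hospitals less one); no new data are needed. Hospitals with only one group contribute nothing to the within-hospital contrast. If the table shows that treatment type is nearly determined by hospital, adjustment cannot rescue the comparison, and the report should state that the two effects cannot be separated.

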**Method/design::**

In total, 180 patients with dementia or MCI will be recruited and will undergo monthly check-up for 12 weeks. Information regarding demographic characteristics, baseline disease-related data, and outcomes related to cognitive function and quality of life will be obtained. For data analysis, the patients will be classified into 2 groups using a comparative observational study design: the sole treatment group, which will receive either WM or KM alone, and the collaborative treatment group, which will receive both WM and KM.

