### Consent and registration

2.3

The subjects are recruited from the OPDs of 7 of the hospitals participating in the pilot project. Independent researchers who are not in charge of the treatment of the subjects inquire regarding the willingness of the subjects to participate in this observational study. The researchers provide the potential subjects with detailed written information regarding the study and provide them with the opportunity to ask questions regarding the study. The researchers emphasize that the patient's participation in this study will not have any effect on his or her treatment. When a subject finally decides to participate in this observational study, he or she will be asked to submit written informed consent. For patients with a limited ability to consent, an explanation of the study will be provided to both the patient and the patient's legal representative and written consent will be obtained from both individuals. In this case, the study will proceed to the next step only when the patient certainly expresses his/her willingness to participate.

After providing written consent, the subjects will be screened for the eligibility criteria. When a subject is judged suitable for participation in the study, he or she will be registered for the study and assigned a registration number.

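### CT and ST are defined by treatment received during a follow-up with free switching and no stated classification time point, and the ITT and per-protocol labels have no assigned or protocol treatment to refer to

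*Protocol article*

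**What the plan says.** **Groups.** The abstract (Method/design) forms the groups at the analysis stage, according to treatment: "the sole treatment group, which will receive either WM or KM alone, and the collaborative treatment group, which will receive both WM and KM".

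**Assignment.** Under Consent and registration (2.3), an eligible patient receives a number and nothing more: "he or she will be registered for the study and assigned a registration number".

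**Treatment.** Section 2.6 says "there is no fixed treatment for the study", and adds: "The participants can freely decide the type of treatment in consultation with their practitioners at any time, as with general care". It also describes the route into collaborative care. "When a participant wishes to receive both WM and KM treatment", a practitioner of one medicine sends a request to a practitioner of the other. The same section says that all treatments received are recorded.

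**Outcome times.** Quality-of-life changes are taken at 4 and 8 weeks (2.5.1.1), cognitive changes at 8 weeks (2.5.1.2) and long-term care items at 12 weeks (2.5.1.3). Follow-up lasts 12 weeks.

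**Analysis.** Section 2.8 prescribes t tests or rank sum tests between the two groups, then: "Per-protocol and intention-to-treat (ITT) analyses will be used to assess all effectiveness and cost-effectiveness data". The text that follows connects ITT with missing data and multiple imputation. It gives no rule for group membership.

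**The concern.** An intention-to-treat analysis keeps patients in the group to which they were assigned, and a per-protocol analysis keeps those who followed a prescribed treatment. This study has neither an assignment nor a prescribed treatment, so the two labels do not say who is analysed in which group.

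The only definition offered is treatment received, and what a patient receives may change during the period in which outcomes are measured. Two problems can follow:

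- A patient who declines by week 4 and then adds the second medicine has received both. Under the received-treatment definition, that decline is counted in CT.
- A patient who adds the second medicine in week 10 has also received both, but every 4- and 8-week outcome was recorded under sole treatment.

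The CT versus ST contrast is the study's stated purpose. Neither adjustment for baseline variables nor multiple imputation corrects a group label that was formed after the outcome began to unfold.

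**Working it through.** **1. The plan's own figure.** Section 2.7 aims for 120 complete cases with 20% missing data: 120 / (1 − 0.20) = 150. This reproduces the stated minimum, but it does not bear on the point. The article gives no effect size, SD or CT:ST ratio, so there is no power figure to reproduce.

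**2. Timing.** For a patient who starts on sole treatment and adds the second medicine during follow-up:

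| Second medicine added | Week-4 outcome | Week-8 outcome | Week-12 long-term care items |
|---|---|---|---|
| Week 2 | after exposure | after exposure | after exposure |
| Week 5 | before exposure | after exposure | after exposure |
| Week 10 | before exposure | before exposure | after exposure |

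All three patients meet the words of the CT definition. Nothing in the text shown separates them.

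**3. Size, by illustration.** From the documents: 120 complete cases and a two-sided 5% test. Assumed, because the documents give no figure: no treatment effect; 30% on CT at baseline (36 CT, 84 ST); correlation r = 0.5 between standardised 4- and 8-week changes; a fraction s of ST patients switch; 80% of switchers come from the half that is worse at week 4.

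The mean of the worse half of a standard normal is −√(2/π) = −0.798, and that of the better half is +0.798. The mean week-8 change among switchers is therefore

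m = r × (−0.798) × (0.8 − 0.2) = 0.5 × (−0.479) = −0.239 SD.

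With k = 84s switchers, apparent CT − ST = k·m/(36 + k) − (−k·m)/(84 − k).

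| s | k | CT mean | Remaining ST mean | CT − ST |
|---|---|---|---|---|
| 10% | 8.4 | −2.01/44.4 = −0.045 | 2.01/75.6 = 0.027 | −0.07 SD |
| 20% | 16.8 | −4.02/52.8 = −0.076 | 4.02/67.2 = 0.060 | −0.14 SD |
| 30% | 25.2 | −6.03/61.2 = −0.099 | 6.03/58.8 = 0.103 | −0.20 SD |
| 40% | 33.6 | −8.04/69.6 = −0.116 | 8.04/50.4 = 0.160 | −0.28 SD |

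Simulation of the same model (3,000 trials per setting) gave −0.14, −0.21 and −0.28 SD at 20%, 30% and 40% switching, with rejection rates of 12%, 20% and 32%. At 10% switching, rejection was about 6%. With the group fixed at baseline it was about 5%. At r = 0.7, the rates for 20%, 30% and 40% switching were 18%, 34% and 57%.

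**4. Sensitivity to the assumptions.** If 60% of switchers come from the worse half, (0.8 − 0.2) becomes (0.6 − 0.4). The bias falls to a third, about −0.05 to −0.07 SD at 20% to 30% switching, and rejection is at most about 6%. If switching is unrelated to early course, it stays at about 5%.

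A second model started 60 patients in each group, drew switchers only from ST patients with below-average week-4 change, and used correlations of 0.3 to 0.7. Rejection was 0.056 to 0.092 with about 6 switchers, 0.076 to 0.240 with about 12, and 0.20 to 0.78 with about 24. Baseline grouping gave 0.045 to 0.054 throughout.

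**The case against.** The strongest reply is that an article condenses a fuller plan. A classification date and a rule for switchers may stand there, or in the flow diagram or schedule, neither of which is shown. ITT may simply mean all enrolled patients with imputation, and per-protocol may mean completers. That reading fits the sentences that follow in section 2.8, so it would be too strong to say that no such analysis sets could be formed. It still leaves CT and ST membership open, and the article does more than stay silent: it fixes grouping by treatment received, allows free switching, and names analysis sets that its design does not define.

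A reader might also infer more than the documents support:

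- **That the groups are formed by the course of the disease.** Section 2.6 permits switching. It does not say how often it happens or that worsening prompts it. Membership can depend in part on early course; no more is shown.
- **That every comparison has exposure after outcome.** The long-term care items at 12 weeks come at the end of follow-up, so that fault does not reach them.
- **That patients treated by another provider will be misclassified as ST.** Section 2.4 says "Administrative data from each institution will be used to determine the costs of MCI/dementia treatments, and the type and frequency of collaborative treatment", but it also lists insurance review (HIRA) data on the types of service used, and section 2.6 says all treatments are recorded. Nothing says that institutional records alone decide the group.
- **That the bias is known to be large.** It is small at about 10% switching, or when switching is only weakly related to early course.

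**Conclusion.** The point stands as a flaw in what the article fixes. Received-treatment grouping, free switching, outcomes inside the switching period and plain two-group tests together allow early worsening to move patients into CT, and allow outcomes to precede exposure. The ITT and per-protocol labels suggest a safeguard that the design lacks.

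The size is not known. Under the main illustration, false rejection rises from about 6% at 10% switching to between 12% and 32% at 20% to 40%. This rests on the assumed 30% CT share, correlation of 0.5 and 80% of switchers from the worse half. The direction, CT looking worse, rests on worsening being what prompts the addition. The baseline-fixed result of about 5% assumes that baseline starters are comparable. Baseline confounding is a separate issue that this correction does not touch. A classification time point in the figure, the schedule or the full plan would narrow the finding.

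**What to change.** 1. Define CT and ST once, from the treatment started or requested at registration. Alternatively, use a short fixed landmark window and count change from its end.
2. For the main comparison, keep each patient in that group whatever happens later. Call it an initial-strategy analysis of all enrolled patients with imputation, in place of ITT.
3. Replace per-protocol with a defined secondary analysis of patients who stay on their initial strategy, labelled as open to selection. Inverse-probability weighting for change of strategy is optional: it needs a model for switching and may be unstable with about 120 complete cases.
4. Report how many patients switch, in which direction and when.

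Items 1, 2 and 4 need plan wording and a group variable derived from treatments that section 2.6 already has recorded. Weighting, if chosen, costs more. The drawback is dilution: if many patients switch, the initial-strategy contrast understates any difference between sustained strategies. A landmark window also leaves out change that occurs before it closes.

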##### QoL

2.5.1.1

Changes in S-IADL, Barthel-ADL, NPI-Q, and S-GDpS scores from baseline to 4 and 8 weeks after the baseline will be used to evaluate effectiveness in terms of QoL.

The S-IADL consists of 15 questions scored from 0 to 3, wherein higher scores indicate more disability in ADL. The questionnaire evaluates current and potential performance separately.^[27]^

The Barthel-ADL is widely used to evaluate ADL because it requires a short time and is easy to score.^[32]^ There are various modifications of the test, including one by Collin et al^[33]^, who simplified the scoring system to range from 1 to 20. The Korean version of the Barthel-ADL has been shown to be valid and reliable.^[29]^

The NPI-Q is used to measure abnormal behaviors. It is read and evaluated by caregivers. The questionnaire can be easily used in the medical field in the real world.^[28]^ The official Korean version of the NPI-Q is used in this study. This version is distributed by the Mapi Research Trust (https://eprovide.mapi-trust.org).

The S-GDpS is used to evaluate the symptoms of depressive mood in elderly individuals. It consists of 15 questions. The Korean version of the S-GDpS is used in this study.^[26]^

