##### Cognitive function

2.5.1.2

Changes in the MoCA-K, MMSE, CDR, and GDS scores from baseline to 8 weeks will be used to evaluate effectiveness in terms of improvement in cognitive function.

The MoCA was created to screen for individuals with MCI, who have normal scores on the MMSE. The questionnaire consists of visuospatial/executive ability, naming, memory, attention, language, abstraction, delayed recall, and orientation domains.^[34]^ The MoCA-K, which is a validated Korean version of the test,^[25]^ is used in this study. We have registered the study on *mocatest.org*.

The MMSE is one of the most broadly used screening tests for dementia. It was created by Folstein et al and can be completed in 5 to 15 minutes. This test has a total score of 30. It has the advantage of being useful in assessing changes over time, based on repeated measures during disease progression. This is because the test only has a small learning effect.^[35]^ The reliability and validity of the MMSE have been demonstrated in distinguishing moderate and severe dementia.^[24]^ The official Korean version of the test, which is supplied by the Psychological Assessment Resources, is used here.

The CDR is the most widely used test to evaluate the severity of dementia. It is divided into the following domains: memory, orientation, judgment and problem-solving, community affairs, home and hobbies, and personal care. Each category is scored on a 5-point severity scale (none, questionable, mild, moderate, and severe).^[36]^ The Korean CDR has been shown to be valid.^[16]^ The score is determined by the doctor, who makes his or her assessment based on detailed examinations of the patient and his or her caregiver.

The GDS is used to evaluate overall cognitive function. It is scored on a scale of 1 to 7 (0, no cognitive decline; 2, very mild cognitive decline; 3, mild cognitive decline; 4, moderate cognitive decline; 5, moderately severe cognitive decline; 6, severe cognitive decline; and 7, very severe cognitive decline).^[37–39]^ The validity of the Korean version of the GDS has been demonstrated.^[23]^

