##### Others

2.5.1.3

“Long-term care score” and “use of long-term care service” will be investigated at baseline and 12 weeks after the baseline. The “use of long-term care service” includes home-visit care, home-visit bathing, home-visit nursing, day and night care, short-term care, and use of geriatric care facilities.

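### Fourteen unranked primary comparisons are each tested at two-sided .05, so the error rate of the effectiveness conclusion is well above 5%

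*Protocol article*

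**What the plan says.** Section 2.5.1 of the protocol article puts three blocks under the single heading of primary outcomes and ranks none of them.

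- Section 2.5.1.1 (QoL): "Changes in S-IADL, Barthel-ADL, NPI-Q, and S-GDpS scores from baseline to 4 and 8 weeks after the baseline will be used to evaluate effectiveness". On the S-IADL it adds: "The questionnaire evaluates current and potential performance separately".
- Section 2.5.1.2 (Cognitive function): "Changes in the MoCA-K, MMSE, CDR, and GDS scores from baseline to 8 weeks will be used to evaluate effectiveness".
- Section 2.5.1.3 (Others): long-term care score and use of long-term care service "will be investigated at baseline and 12 weeks after the baseline".

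Section 2.8 compares the collaborative and sole treatment groups variable by variable, with t or Wilcoxon tests for continuous variables and chi-square or Fisher tests for categorical ones. It sets one error level for everything: "All statistical analyses will be performed using 2-tailed tests at a significance level of .05". On analysis sets it says: "Per-protocol and intention-to-treat (ITT) analyses will be used to assess all effectiveness and cost-effectiveness data". Its list of variables to be compared includes the eight primary scales and the use of long-term care service, but not the long-term care score.

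The sample size in section 2.7 rests on a target of 120 complete patients and is not tied to any outcome, effect size or power.

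**The concern.** The introduction asks a comparative question: whether collaborative treatment is more effective and more cost-effective than either system alone. For the effectiveness part, the plan offers more than a dozen primary comparisons of equal standing. It does not say how many must succeed, or which one decides.

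As written, one nominally significant scale at one visit could be reported as a positive primary result. The .05 in section 2.8 is the error rate of each test, not of the conclusion that readers will draw from the whole set. The conclusion is meant to inform how the national health system handles dementia care, so that difference matters.

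**Working it through.** **Inputs from the article.** Two-sided .05 for every test (section 2.8). Outcomes and time points from sections 2.5.1.1 to 2.5.1.3. The article states no familywise error rate, so there is no planned figure to reproduce.

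**Count of primary comparisons.**

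- Quality of life and function: 4 scales × 2 time points = 8
- Cognition: 4 scales × 1 time point = 4
- Long-term care: score and use at 12 weeks = 2
- Total: 8 + 4 + 2 = 14, or 13 if the long-term care score is not tested

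**Independent tests, no treatment effect, no confounding.** The chance of at least one false positive is 1 − (1 − 0.05)^k.

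- k = 14: 1 − 0.95^14 = 0.512; expected false positives 14 × 0.05 = 0.70
- k = 13: 1 − 0.95^13 = 0.487; expected false positives 13 × 0.05 = 0.65

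**Correlated tests.** Independence is not realistic. Several scales measure neighbouring things, and four are repeated at two visits. The article gives no correlations, so the values below are assumptions. The figures come from simulating 400,000 sets of equicorrelated normal test statistics under the global null.

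| Assumed pairwise correlation | 14 tests | 13 tests |
|---|---|---|
| 0 | 51% | 49% |
| 0.3 | 44% | 42% |
| 0.5 | 35% | 34% |
| 0.7 | 25% | 24% |
| 0.9 | 14% | 14% |

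A more structured pattern, with two visits of one scale correlated 0.5 to 0.8 and different scales correlated 0 to 0.5, gives 35% to 50% for 14 tests.

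**Effect of a correction.** Under the global null, Holm makes a false claim only if the smallest p-value falls below 0.05/14 = 0.00357. With 14 independent tests the familywise error is 1 − (1 − 0.00357)^14 = 0.049. At correlations of 0.3, 0.5 and 0.7, the simulation gives 4.5%, 3.8% and 2.7%.

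**What a correction costs in power.** As an illustration, assume the 120 complete patients split 60/60 (the article fixes no split) and a true difference of 0.5 SD. A single test at .05 has 78% power. At 0.00357, the strictest Holm step, power is 43%.

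**The case against.** **The study is observational and modest in its claims.** It is a registry-based study with a recruitment-driven sample size, and the Discussion describes its data as basic reference information for later work. Whether such a study needs familywise control is debated. This lowers the weight of the point but does not remove it: the introduction states a comparative question, the tests are not labelled exploratory, and the outcomes are labelled primary.

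**Testing order is often left to a statistical analysis plan, which is not shown.** That would answer a complaint about silence. Here the article itself fixes .05 for all analyses and gives all these outcomes primary status. A later adjustment would have to depart from the published rule.

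**Confounding is the larger threat.** Patients choose their treatment and may change it at any time, and section 2.8 describes unadjusted two-group tests. This stands. The percentages above assume no confounding; with it, even a single primary test would not have a 5% error rate.

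**Stronger readings that the article does not support.**

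- *A false-positive primary result is more likely than not.* Only near-independence gives about one half. With correlated scales, one in three to one in two is the fairer range.
- *There are at least 14 tests, or 16 with both S-IADL scores.* Section 2.8 explicitly lists only 13 of the 14. Section 2.5.1.1 says that the instrument rates current and potential performance separately, not that both are endpoints.
- *Two analysis sets double the risk.* The ITT and per-protocol sets share most patients, so their results are highly correlated and the added risk is far less than double. The problem is that neither is named as the main one.
- *The article points to MoCA-K as the natural single primary.* Section 2.5.1.2 describes the MoCA as a screening tool for MCI and credits the MMSE with usefulness in tracking change. Eligibility also extends to dementia with a CDR of up to 2.0.

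**Conclusion.** The point holds. There are 14 unranked primary comparisons (13 if the long-term care score is not tested), each at two-sided .05, with no hierarchy, adjustment or success rule. If collaborative treatment had no effect and the groups were otherwise comparable, the chance of at least one false-positive primary result would be about 49–51% under independence, about 35–44% at correlations of 0.5 to 0.3, and 25% at 0.7. The exact figure depends on correlations that the article does not give, but it stays well above 5% across the whole range examined, including 14% at a correlation of 0.9.

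This is a point that should be fixed, not one that invalidates the study. It concerns the error rate of the primary effectiveness claim only. The figures say nothing about bias from self-selected treatment, and correcting multiplicity would not control that bias.

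**What to change.** Amend sections 2.5.1 and 2.8 in one of two ways.

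1. Name one primary outcome, at one time point, in one named analysis set. Make the other scales, visits and long-term care items secondary or exploratory, reported with estimates and 95% confidence intervals. The choice of scale is the sponsor's.
2. Keep several primaries, list exactly which comparisons belong to the set and in which analysis set they are judged, and apply Holm across them at .05 overall.

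Either way, state whether the long-term care score is tested, since sections 2.5.1.3 and 2.8 differ on this. If the S-IADL is kept as a primary, state which of its scores is meant.

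The study is under way and registered, so the choice should be made without sight of results by group, recorded with a date, and carried into the registry record.

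No new data are needed. The cost of the first option is that fewer outcomes can be headlined as primary. The cost of the second is lower power per outcome, which shrinks as the list of primaries is shortened. Adjustment for confounding needs its own treatment in the plan.
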